#### Plans to give access to the full protocol, participant level-data, and statistical code {31c}

Access to the datasets used and analysed during the study are available in a fully anonymised form from the sponsor on reasonable request.

### Oversight and monitoring

#### Composition of the coordinating centre and trial steering committee {5d}

The ADAPT Trial Management Group consists of the sponsor and the coordinating investigator. They are responsible to ensure that collaborative sites adhere to the study protocol, the appropriate contact to authorities, and appropriate data management and analyses. The ADAPT Trial Management Group will be available by e-mail or phone in case of urgent problems or concerns relating to the trial.

As a part of networking, investigators and collaborating colleagues will be invited for a yearly, half-day seminar to receive an update on the trial and to discuss relevant new research in nephrotic syndrome and MCN.

#### Composition of the data monitoring committee, its role and reporting structure {21a}

The trial has no attached Data Management Committee. The ADAPT Trial Management Group will supervise and monitor data collection and the reporting structure in corporation with the authorities (e.g. Good Clinical Practice (GCP) units). The potential benefits from reducing cumulative prednisolone dose are believed to override the risk of failure to achieve remission in the lower prednisolone dose regimen. Data uploaded in eCRF (RedCap) will continuously be monitored by the ADAPT trial Management Group and by the Good Clinical Practice (GCP) units in Denmark during the trial period.

### Adverse event reporting and harms {22}

Subjective events during the trial will be reported by patients in questionnaires (SF36 and Cushing QoL). Local investigators will report adverse events after results of blood test (development of diabetes, infections, hyperlipidaemia), examinations (hypertension, weight gain, skin toxicity), and questionnaires (glucocorticoid toxicity index). All the events will be collected and stored in RedCap. In case of severe adverse events, the sponsor will be informed and report it to relevant authorities.

### Frequency and plans for auditing trial conduct {23}

The ADAPT Trial Management Group will continuously be auditing the trial conduct by conversations and meetings with the local investigators and by monitoring data reporting in RedCap. During the trial period, the coordinating investigator will be in close contact with all the sites, and in case of difficulties of any kind, the coordinating investigator will contact the relevant site investigator to resolve the issue to make sure of optimal trial conduct.

### Plans for communicating important protocol amendments to relevant parties (e.g. trial participants, ethical committees) {25}

In case of protocol modifications, all relevant parts will be informed by e-mail or phone.

### Dissemination plans {31a}

The results of the trial, positive as well as negative, will be submitted to peer reviewed, international journals and presented at conferences and meetings. The participants will be informed on the patients’ association “Nyreforeningens” website (www.nyre.dk).

## Discussion

Lower dose of prednisolone in combination with active vitamin D in MCN might be an applicable option for sufficient disease control as a few small randomised studies suggest [14, 32–34].

Patients with MCN and nephrotic syndrome often have no co-morbidities. When being diagnosed with MCN, they experience symptoms such as oedema, fatigue, and foaming urine. After initiating medical treatment, they often experience additional changes and events, which can be related to both the disease and the treatment strategy. Is it imperative that we trace a treatment strategy that is minimising treatment-related adverse events.

This trial uses a predefined electronic randomisation open-labelled design. The open-label design reflects the daily clinically reality. Adherence to treatment strategy and patient compliance will be monitored, e.g. by counting pills. It is commonly anticipated that lower dose of prednisolone decreases adverse events. This might encourage a speedy reduction of prednisolone dose or cross-over from standard to reduced dose of prednisolone especially if the patient prior to treatment has obstacles with e.g. obesity, osteoporosis, hypertension or other known adverse events to prednisolone treatment. Local investigators will be encouraged to adhere to treatment strategy and change in prednisolone dose can only be done after agreement with sponsor or his substitute. The trial will provide evidence to the commonly anticipated belief that the number of adverse events increases with the dose of prednisolone. Alfacalcidol is a well-known treatment among nephrologists and widely used in other patients with chronic nephropathies. Using it in patients with MCN is newfound but expected to be tolerable.

Self-reported, prednisolone associated adverse events have not been systematically evaluated in MCN, but in renal transplant patients, the cumulative dose of prednisolone correlates with reported adverse effects using the Cushing QoL questionnaire [26, 27] and SF36 [35].

This trial should allow us to determine if low dose prednisolone in combination with active vitamin D is clinically as efficient as current standard therapy to induce remission in MCN with the potential to reduce significant adverse events. This may lead to changes of current guidelines for the treatment of MCN. If so, the results potentially can inspire to additional trials in other prednisolone-treated diseases to examine reduced dose of prednisolone.

Furthermore, the trial should provide additional information on the ability of a saliva test to characterise prednisolone pharmacokinetics in individuals and the ability of this to predict the prednisolone dose-dependent treatment response. In the future, such tests may allow for a more personalised treatment and dosing regimen not only in patients with MCN but also in other patients requiring prednisolone treatment.

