Treatment with prednisolone is associated with important physical and mental adverse effects, including an increased risk of infections, obesity, diabetes, and hypertension and mental changes, e.g. mood changes, depression, and agitation [24], which collectively constitute a strong argument for reducing the cumulative prednisolone dose. Recently, a Glucocorticoid Toxicity Index [25] has been developed to identify and quantitate prednisolone-related complications. The Index includes changes in body mass index, glucose tolerance, blood pressure, lipid status, bone density, steroid myopathy, skin toxicity, neuropsychiatric toxicity, infections, and adrenal insufficiency, as well as gastrointestinal and ocular disease. The Cushing Quality of life (QoL) questionnaire addresses known problem areas in Cushing and is useful for evaluating patient-reported health-related quality of life and correlates with clinical parameters [26, 27]. Also, the short form (SF) 36 is a well-established patient-reported survey that has been used to determine the health-related QoL in the general population and among different groups of patients, e.g. patients with renal disease [28].

The pharmacokinetics of prednisolone are complex. Prednisolone is protein bound, and its metabolism is influenced by gender and plasma albumin as well as by liver function and genetic variations in the enzymes CYP3A4, CYP3A5, ABCB1, and NR112 [29]. Repetitive samplings of non-stimulated saliva provide a good estimate of prednisolone turnover in healthy people [29] and in children with nephrotic syndrome [30]. This may allow for individualised dosing of prednisolone to reduce adverse events without compromising efficacy.

The aim of this study is to test the hypothesis that a new treatment regimen in MCN combining reduced dose prednisolone and active vitamin D is as efficient in inducing remission and has fewer and less severe adverse events than standard prednisolone. Furthermore, we aim to establish models allowing for more personalized medicine based on assessment of the individual’s prednisolone metabolism.

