### Objectives {7}

Based on the potential benefits from reducing cumulative prednisolone dose and the possible positive effects of active vitamin D in nephrotic syndrome, the study will test the following hypothesis:
Treatment of MCN with a reduced dose of prednisolone in combination with active vitamin D is non-inferior to standard dose of prednisolone with respect to rate and time to remission.Treatment of MCN with a reduced dose of prednisolone in combination with active vitamin D reduces the incidence of both the observed and subjective adverse events compared with the standard dose of prednisolone.Patients with MCN and a fast turnover of prednisolone have a lower rate of remission, longer time to remission, and fewer adverse events than patients with a slow turnover of prednisolone.

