### Outcomes {12}

Remission is defined by a urine-protein/creatinine ratio < 0.4 g/g and/or a urine-albumin/creatinine ratio < 0.3 g/g on two consecutive tests.

Relapse is defined as the recurrence of proteinuria, i.e. a urine-protein/creatinine ratio > 0.75 g/g and/or urine-albumin/creatinine ratio > 0.5 g/g in two consecutive tests and a decline in p-albumin of > 3 g/l.

Primary endpoints:
Rate of remissions after 16 weeks.Time from diagnosis to remission.

Secondary endpoints:
Rate of relapse within 1 year after remission.Time from remission to relapse.Rate of adverse events and number of hospital admissions.The associations between genetic variations in liver enzyme genes, the concentration of prednisolone in saliva, and remission or relapse.

Safety endpoints:
Patient survivalAcute kidney injury (AKI stage 2 or 3 as defined by KDIGO [31])Serious infections requiring admissionPersistent hypercalcaemia (> 2 weeks) defined by an elevated plasma-ionised-calcium and not normalising by reducing alfacalcidol dose.Severe adverse effects to prednisolone, e.g. gastrointestinal bleeding and severe depression

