### Statistical methods

#### Statistical methods for primary and secondary outcomes {20a}

The primary endpoints are analysed as intention-to-treat. Since this is an open-label study, there is a risk of cross-over between the two intervention groups, but we expect high adherence to intervention groups. Anyway, additional treated-as analyses will be included. Secondary endpoints are analysed as differences in absolute and relative proportions. Factors affecting the primary endpoint (age, baseline eGFR, albuminuria, prednisolone dose or alternative saliva profile) will be identified using a generalised, linear model.

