#### Methods for additional analyses (e.g. subgroup analyses) {20b}

Not applicable.

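### The personalisation aim goes beyond the analyses named, and saliva concentration entered without randomised arm mixes the dose difference with individual metabolism

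*Protocol article*

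**What the plan says.** All references are to the Protocol article.

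- **Aim.** Background and rationale {6a} (and the Abstract) states: "we aim to establish models allowing for more personalized medicine based on assessment of the individual’s prednisolone metabolism". The Discussion adds that the trial should inform on the saliva test and "the ability of this to predict the prednisolone dose-dependent treatment response".
- **Formal hypothesis.** Objectives {7}, third item, is narrower: "Patients with MCN and a fast turnover of prednisolone have a lower rate of remission, longer time to remission", and fewer adverse events, than with slow turnover.
- **Secondary endpoint.** Outcomes {12}: "The associations between genetic variations in liver enzyme genes, the concentration of prednisolone in saliva, and remission or relapse".
- **Model.** Statistical methods {20a}: "Factors affecting the primary endpoint (age, baseline eGFR, albuminuria, prednisolone dose or alternative saliva profile) will be identified using a generalised, linear model".
- **Other saliva analysis.** Section {18a} compares saliva concentrations with remission, relapse and adverse events and does not mention arm. Sampling is about 4 weeks into prednisolone, before tapering.
- **Additional or subgroup analyses.** Section {20b}: "Not applicable".
- **Arms.** Trial design {8}: 1 mg/kg/day (maximum 80 mg/day) against 0.5 mg/kg/day plus alfacalcidol.

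**The concern.** Predicting a dose-dependent response is a question of effect modification: does the difference between the randomised regimens change with a patient's turnover? No analysis named in the article estimates that.

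There is also a problem with the narrower third hypothesis. Turnover is a property of the patient. A concentration measured on treatment reflects both the patient and the dose. If saliva profile stands in for dose, and arm is not in the model, an effect of regimen (dose or alfacalcidol) can appear as an effect of metabolism, or a real effect of metabolism can be diluted by dose-driven spread. If the reduced regimen did worse, low saliva concentration would go with fewer remissions even if metabolism played no part, which would look like support for the third hypothesis.

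**Working it through.** The protocol gives no figure for this aim. Its only sizing, 43 completers per group and 96 recruited, is for the non-inferiority comparison. Inputs from the protocol are 96 patients, 86 completers, 1:1 allocation, 80% remission at 16 weeks on standard treatment, a nominal twofold dose ratio and saliva at about week 4. Everything else below is an assumption.

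**1. How much of saliva concentration is dose.** Assume concentration is proportional to dose and that log concentration has a between-patient SD of s within arm. With 1:1 allocation the dose difference adds variance (ln 2 / 2)² = 0.120. Its share of the total is 0.120 / (0.120 + s²):
- s = 0.25: 0.120 / 0.1825 = 66%
- s = 0.4: 0.120 / 0.280 = 43%
- s = 0.8: 0.120 / 0.760 = 16%

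The protocol does not give s.

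**2. False attribution to metabolism.** Assume remission of 80% v 60% by arm and no effect of metabolism, with 96 patients. A model with saliva alone was significant at 0.05 in 28% of simulated trials; with arm added, in 4.5%. The rate falls as the spread widens. A logistic model with saliva alone gave about 40%, 26% and 13% at s = 0.25, 0.4 and 0.8, so 28% belongs to a spread a little under 0.4. With arm included the rate stayed near 5% throughout.

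**3. What a model without the product term can show.** Assume exponential remission times, 80% by week 16 at average turnover, and Cox models with arm and standardised turnover.
- Scenario A, log-HR −0.25 per SD in both arms: pooled turnover HR about 0.78.
- Scenario B, 0 in standard and −0.5 in reduced: pooled HR about 0.78.

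The pooled estimate does not separate them, although in B the regimens differ greatly by turnover. Reduced-arm remission at week 16 is 1 − 0.2^exp(0.5) = 93% at −1 SD and 1 − 0.2^exp(−0.5) = 62% at +1 SD, against 80% at any turnover in the standard arm. Adding the product term recovers arm HRs of about 1.00 and 0.59.

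**4. Power of the product term** (two-sided 0.05).
- The SE is about 0.25. Simulated power for an interaction of 0.5 is about 55% with 96 patients and about 50% with 86.
- Half that interaction: Φ(0.25/0.25 − 1.96) = Φ(−0.96) = 17%.
- Week-4 landmark: 1 − 0.2^(4/16) = 33% have already remitted. Remissions by week 16 fall from 96 × 0.80 = 77 to 96 × (0.80 − 0.33) = 45. The SE becomes 0.25 × √(77/45) = 0.327, and power Φ(0.5/0.327 − 1.96) = Φ(−0.43) = 33%.
- Binary version (remission at 16 weeks, fast v slow split 50/50, 86 completers, 21.5 per cell, 80% in three cells): for a 20-point interaction SE = √[(0.24 + 3 × 0.16)/21.5] = 0.183 and power is Φ(0.20/0.183 − 1.96) = 19%. For 10, 30 and 40 points it is 8%, 37% and 59%.

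**The case against.** The case against has real weight.

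- **The formal objective is prognostic.** The third hypothesis and the secondary endpoint ask for associations, and section {18a} plans them. The Discussion promises only additional information and places individual dosing in the future. This stands. It means the aim could be narrowed instead of the analysis widened.
- **A reader might infer that the plan fixes a main-effects model and forbids anything else.** The document does not say so. A generalised linear model can carry a product term, the SAP and full protocol are not shown, and the entry in {20b} says only that nothing is listed there. What does stand is that the article names dose or saliva as alternatives and answers the additional-analyses item in the negative, which does not fit its own aim.
- **The alternative may be a deliberate exposure-response model**, with measured exposure replacing nominal dose. That is a legitimate model of exposure. It does not isolate turnover, and without arm it also absorbs any effect of alfacalcidol.
- **The simulation in step 3 is not the model in {20a}.** Correct: it enters arm and turnover together, which is more favourable than the plan, and scenario B is an assumed, large effect. It shows what pooling loses, not what this trial will find.
- **A reader might infer that randomisation gives an unconfounded answer on dose.** It does not: the arms also differ by alfacalcidol. Turnover is measured after randomisation, and {6a} says prednisolone metabolism is influenced by plasma albumin, so measured turnover may partly reflect response.

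**Conclusion.** The mismatch holds. The aim reaches to predicting dose-dependent response, while the named analyses are associations not separated by arm and a model in which saliva may replace dose. Followed literally, they neither test turnover cleanly nor show whether the regimen difference varies with it. The size depends on the spread of saliva concentration: dose accounts for 16% to 66% of its log variance for s from 0.8 down to 0.25, and false significance was 28% in the scenario of step 2. That false significance requires a real difference between regimens; if they are equally effective, the harm is dilution instead.

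A reader might go further and conclude that the trial cannot say who needs which dose. That is too strong. The limit lies in the named analysis: two randomised regimens with saliva and genotype data allow an interaction estimate, though an imprecise one, and the protocol does not promise a dosing rule. The point concerns a secondary aim and leaves the primary comparison untouched.

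**What to change.** 1. In {20a}, replace the alternative between dose and saliva with randomised arm plus dose-normalised turnover (continuous) in the same model.
2. In {20b}, replace the present entry with one pre-specified exploratory analysis, the arm-by-turnover product term. Report turnover slopes by arm with 95% CI.
3. For time to remission, start follow-up at the saliva sample (landmark or delayed entry), so that patients are not counted as at risk before their turnover is known.
4. Use baseline genotype as a companion marker, since it is free of post-randomisation influence.
5. Label the result regimen-by-turnover, not dose-by-turnover, and state the low power given above.
6. If this is not wanted, limit the Abstract, {6a} and the Discussion to prognostic association. The arm term in item 1 is still needed for the third hypothesis.

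The cost is one extra model and one table, with no new patients or samples. The downside is an imprecise exploratory estimate and the loss of early remitters from the landmark analysis, about a third under the exponential assumption.

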## Trial status

Currently version of protocol: Version 10.01.2020

Recruitment began in May 2018 and is expected to be completed by 2023.

## Data Availability

Not applicable.

## Abbreviations

ADAPT: (name of the trial) Activated vitamin D and prednisolone treatment
MCN: Minimal change nephropathy
eGFR: Estimated glomerular filtration rate
KDIGO: Kidney Disease: Improving Global Outcomes
QoL: Quality of life
SF 36: Short form 36
CKD-EPI: Chronic Kidney Disease Epidemiology Collaboration
eCRF: Electronic case report file
RedCap: Research Electronic Data Capture
